Mixed methods study of engagement in behaviors to prevent type 2 diabetes among employees with pre-diabetes, 2016 [16]	﻿University of Michigan	Pre and post mixed methods study	﻿Facilitators of and barriers to engagement in recommended behaviors	82 (23 M, 59 F)	3 months	N/A	﻿Key facilitators of engagement included assistance and encouragement from social networks as well as use of external supports such as tracking devices. Barriers to engagement included competing demands and insufficient resources ﻿for healthy behaviors.

Beginning in 2018, the UC System  implemented the UC DPP Initiative, which is a multi-component program to target diabetes and obesity prevention among at risk affiliates. This initiative was informed by a pilot DPP implemented at the University of California Los Angeles (UCLA) in 2016. UCLA DPP was one of the first university-based programs in the US to achieve full CDC recognition. CDC recognition is granted to programs that meet all recommended milestones for DPP delivery, including 5% mean weight loss among participants. Based on the success of the UCLA campus-wide DPP, campus leaders and researchers partnered with the UC Office of the President (UCOP) and UC Health to launch a UC-wide DPP Initiative in 2018. By 2019, all 10 UC campuses had implemented UC DPP, which now operates as part of routine campus activities (more details below). To our knowledge, this is one of the largest university-based efforts to adress diabetes and obesity prevention with a focus on system-wide DPP-based ILI delivery.

Our goal is to conduct a rigorous, mixed-methods evaluation of the UC DPP Initiative, focusing on the five UC campuses with large medical centers where robust EHR data for UC beneficiaries is also available; namely UC Los Angeles, Irvine, San Diego, San Francisco, and Davis. Our goals are to identify why the UC DPP Initiative succeeds (or not), and to document lessons learned across the UC system and between campuses to inform future efforts across UC and other large university systems.

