### The University of California Diabetes Prevention Program (UC DPP) initiative

The UC DPP Initiative has four key components; 1) identification of diabetes prevention as a system-wide goal, 2) a prediabetes awareness campaign targeting at-risk beneficiaries, 3) coordinated DPP implementation and delivery on every UC campus 4) coverage of DPP for all campus affiliates, including faculty, staff and students, at no cost. Each campus identified local champions, engaged key stakeholders, and signed a Memorandum of Understanding (MOU) with UCOP to receive funding for program implementation. The MOU outlined a commitment to the goals of the initiative, delineated guidelines for DPP delivery, and confirmed available resources. Funding to campuses was based on fixed costs of delivering a DPP cohort (i.e., not based on number of participants or program outcomes). Although the UC system could have easily continued to outsource DPP delivery (as many universities and workplaces do through their insurers), this initiative aimed to prioritize diabetes prevention as a highly visible system-wide goal that leverages university-based infrastructure and resources to implement all four key components. For example, campuses aimed to implement > 4 DPP cohorts in their first 2 years and then receive additional UCOP funding to add cohorts based on local demand.

The UC DPP Coordinating Center was established by UCOP/UC Health to support system-wide DPP activities. The UC DPP Coordinating Center assists UC campuses with all aspects of program delivery, including DPP coach training by UCLA-based certified master trainers and data management for DPP cohorts. Centralizing some activities, such as coach training, provides efficiency of scale (e.g., each individual campus is not required to spend time and money to train master trainers). The Coordinating Center leads monthly group calls with all UC campuses and individual calls with each campus as needed. Each UC campus is also registered with the National DPP (each campus has their own unique CDC organization number in order to be eligible for CDC recognition).

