The UC system, like many other academic institutions, provides and manages health insurance benefits for many of its employees. The UC DPP Coordinating Center conducts outreach to at-risk UC health insurance beneficiaries with documented prediabetes (i.e., prediabetes diagnosed as part of usual care). Trained UCOP staff use UC EHR and claims data algorithms to identify at-risk participants with documented prediabetes. Personalized initiation letters with UC DPP logos are mailed from the Coordinating Center to overweight/obese UC beneficiaries with documented prediabetes. These prediabetes awareness letters include information about the importance of diabetes prevention and the UC DPP Initiative, including contact information for the local campus DPP. The letters clarify that there is no out-of-pocket cost for the UC DPP. UC DPP cohorts are led by UC staff who complete DPP coach training and have experience delivering campus-based wellness programs. DPP eligibility criteria include 1) age > 18 years, 2) body mass index (BMI) > 25 kg/m^2^ (> 23 for Asian adults) and 3) history of prediabetes, gestational diabetes, or a “high risk” CDC Prediabetes Risk Test. UC funding is provided to campuses for each additional DPP cohort and is not contingent on meeting National DPP metrics (e.g., 5% weight loss).

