### Data collection & statistical analyses

To measure mean percent weight change, we will use EHR weights, which are collected similarly across UC health center visits, and DPP session weights for UC beneficiaries who enroll in DPP. Baseline covariate differences between those with and without attrition will be examined and we will then adjust for any covariates found to be significantly different (*p* < 0.05) between attrition groups in order to satisfy the Missing at Random assumptions of the mixed effects models. Because attrition could be a consequence of our primary outcome (i.e. weight) our missing data may be Missing Not at Random. In this instance we will utilize pattern mixture modeling to impute missing valuies. We will conduct within-subject analysis estimates of UC DPP Initiative effectiveness among those who received a “full intervention dose” (i.e., Group 1 prediabetes awareness letters and enrolled in DPP). For this primary analysis, we will use a mixed effects linear regression model to compare percent weight change within Group 1 subjects 12 and 24 months before DPP enrollment (pre period) and 12 and 24 months after enrollment (post period). Models for the trajectory of percent weight change will be specified with a random intercept for person with nested random slope for time from enrollment measured on a continuum. Average within-person between time-period (post vs. pre-enrollment) differences in the trajectory for % weight change will be modeled using a fixed effect interaction term of time-by-time-period to test for between time-period differences in the rate of % weight change. These models will be fit using a random intercept for person and random slope for time-period (post vs pre). A fixed effect of time-period will be used to estimate the average between time-period difference in % weight change adjusting for the corresponding length of time over which the change was observed. For both models, exploratory post-hoc analyses will also consider additional subject level covariates (age, gender, race, ethnicity, number of co-morbidities, number of DPP sessions attended, education level and years employed at the institution), as well as DPP site. Interactions of the difference over time (rates or mean levels) by these subject characteristics or site will also be explored to evaluate whether there is a differential benefit of the program for certain groups of beneficiaries (i.e., heterogeneity in treatment effect) and across sites. In the presence of statistically significant (*p* < 0.05) interactions, the models will be stratified so as to allow for potential heterogeneity in the covariates as well.

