### Sample size and power calculations

For our primary outcome of % weight change at 12-month follow-up within subjects, we will use 5% weight change to estimate power based on the 2002 DPP randomized controlled trial [4] as well as National DPP recognition standards [22]. With a proposed sample size of *N* = 50 using a two-sided alpha level of 0.05, we would demonstrate 80% power to detect a paired difference of at least 3.3% and have > 98% power to detect our target weight change of 5%. For our outcome of weight change at 12-month follow-up between subjects, we conservatively assume that the average % weight loss for those in Group 2 (prediabetes notified) and Group 3 (usual care) will be 2 and 0% respectively. These values will yield about a 3% difference in weight loss between our comparison groups. Using an independent samples t-test as a simplification of the mixed effects analysis plan with a two-sided alpha of 0.05, we will have 90% power to detect our assumed between group difference of 3% with the proposed sample sizes of 50 (Group 1; 10 per site) and 500 (Group 2; 100 per site). Using the same assumptions, the proposed sample sizes of *N* = 550 Group A + B and *N* = 500 Group 3 would yield 99% power to detect the assumed 3% difference in the percentage weight change between the groups. We would additionally have 80% power to minimally detect a between group difference of 2.5 and 1.1% with these sample sizes. All sample sizes account for an anticipated 20% loss to follow-up [7]. We will not be powered to detect differences in rates of incident type 2 diabetes, but we will examine trends over time using validated EHR and claims data algorithms [23, 24]. Metformin is not specifically highlighted in the UC DPP Initiative, but since some beneficiaries with prediabetes may also seek out this option, [4, 25] we will also examine rates of metformin uptake using prescription data available in the EHR.

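### Group 1 receives DPP in coach-led cohorts, but the primary and Group 1 vs 2 models and the power treat its members as independent; the effect is modest unless each campus is a single cohort

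*Protocol article*

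**What the plan says.** The initiative section of the protocol article describes group delivery: "UC DPP cohorts are led by UC staff who complete DPP coach training and have experience delivering campus-based wellness programs". It also says that "campuses aimed to implement > 4 DPP cohorts in their first 2 years". The evaluation covers five of the ten campuses (Background: "focusing on the five UC campuses with large medical centers").

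Under Data collection & statistical analyses, the trajectory model has a "random intercept for person with nested random slope for time from enrollment measured on a continuum". For the period comparison, "These models will be fit using a random intercept for person and random slope for time-period (post vs pre"). The Group 1 vs 2 comparison reuses these models with an added interaction for group. DPP site is named only among the exploratory post-hoc covariates and interactions. Cohort and coach appear in no model.

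Under Sample size and power calculations, the primary power is for a paired difference with N = 50: 80% at 3.3% and more than 98% at 5%. The between-group power is obtained "Using an independent samples t-test as a simplification of the mixed effects analysis plan", with "proposed sample sizes of 50 (Group 1; 10 per site) and 500 (Group 2; 100 per site"): 90% at 3% and 80% at 2.5%. No ICC or design effect is mentioned.

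**The concern.** After enrolment, members of one cohort share a coach, a schedule and each other's company. If some cohorts do better than others, their members' changes move together. The person intercept and the person slope for period let each person have an own level and an own change, but they leave the changes of different persons independent. A cohort effect on the post-enrolment change therefore passes straight into the pre/post contrast, which is the primary estimate, and into Group 1's side of the Group 1 vs 2 contrast, without being counted in the standard error.

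This is more than detail left to an analysis plan, because the article commits to a random-effects structure and gives site an exploratory role. Intervals and p-values for the primary and the Group 1 vs 2 contrast would be too optimistic to the extent that cohorts differ in change.

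**Working it through.** **Step 1: reproduce the stated power.** The article gives no SD, so it is back-solved from one power figure and checked against another (two-sided alpha 0.05).

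- Primary, paired: 80% at 3.3% with N = 50 implies an SD of change of 8.16. Power at 5% is then 98.9%, which matches the stated figure of more than 98%.
- Group 1 vs 2, normal approximation: sqrt(1/50 + 1/500) = 0.1483. From 80% at 2.5%, SD = 2.5/(2.80 × 0.1483) = 6.0. From 90% at 3%, SD = 3/(3.24 × 0.1483) = 6.2. The value 6.1 lies between them and is used below. It gives Phi(3/(6.1 × 0.1483) − 1.96) = 91% with no clustering.

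The stated figures therefore match calculations on independent persons with no design effect.

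**Step 2: cluster size.** This is an assumption. About four cohorts at each of five campuses is 20 cohorts, and 50/20 = 2.5 Group 1 members per cohort. The upper bound is one cohort per campus, so m = 10. The article does not say how the 50 are spread.

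**Step 3: ICC of the pre-to-post change.** This is also an assumption: 0.02, 0.05 and 0.10.

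**Step 4: formulas.**

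- Design effect: DE = 1 + (m − 1) × ICC.
- Type I error of the unadjusted within-Group 1 test: 2 × (1 − Phi(1.96/sqrt(DE))).
- Paired detectable difference at 80% power: 3.3 × sqrt(DE).
- Paired power at 5%: noncentral t with SD 8.16 × sqrt(DE) and 49 df.
- Group 1 vs 2 power at 3%: Phi(3/(6.1 × sqrt(DE/50 + 1/500)) − 1.96).

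| m | ICC | DE | Type I error | Paired detectable difference | Paired power at 5% | Group 1 vs 2 power at 3% |
|---|---|---|---|---|---|---|
| 2.5 | 0.02 | 1.03 | 5.3% | 3.35% | 98.7% | 90.5% |
| 2.5 | 0.05 | 1.075 | 5.9% | 3.42% | 98.4% | 89.4% |
| 2.5 | 0.10 | 1.15 | 6.8% | 3.54% | 97.7% | 87.5% |
| 10 | 0.02 | 1.18 | 7.1% | 3.58% | 97.4% | 86.7% |
| 10 | 0.05 | 1.45 | 10.4% | 3.97% | 94.1% | 79.8% |
| 10 | 0.10 | 1.90 | 15.5% | 4.55% | 86.9% | 69.1% |

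Worked row (m = 2.5, ICC 0.05): DE = 1 + 1.5 × 0.05 = 1.075; 1.96/sqrt(1.075) = 1.890, giving 5.9%; 3.3 × 1.037 = 3.42.

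**Step 5: loss to follow-up.** If the 50 shrink to 40 completers over the same 20 cohorts, m = 2 and DE is 1.02 to 1.10 for the same ICC range, so the picture is unchanged.

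**Step 6: Groups 1 + 2 vs 3.** Only 50 of 550 are in cohorts. Even at DE = 1.90, the variance factor goes from 1/550 + 1/500 = 0.00382 to (50 × 1.90 + 500)/550² + 1/500 = 0.00397. The standard error rises by about 2%.

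**The case against.** The case on the other side is about size and about which level clusters, and much of it stands.

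- **Cluster size.** Taking m = 10 treats a campus as one cohort, while the article plans several cohorts per campus. On that plan the effect is slight. This stands, and m = 10 can serve only as an upper bound.
- **Campus as a cluster.** A reader might infer that 10 people per campus in itself makes the standard errors too small. The documents do not support that. The five campuses are a named set with 10 Group 1 members each. If they are treated as fixed, omitting campus leaves between-campus differences in the residual, so the standard error of the average change is if anything slightly too large. Stable campus differences also cancel in the pre/post contrast.
- **The power method.** A reader might take the independent t-test to underlie the primary power. It does not: that calculation is paired, and the t-test is an acknowledged simplification for the between-group contrasts only. The acknowledgement does not settle the point, however, because the mixed model being simplified has no cohort term either.
- **Site is not ignored.** Site covariates and interactions are planned, with stratification where these are significant. They are exploratory and concern site, so they do not correct the primary standard error for cohort.
- **Estimability.** A cohort variance from about 20 groups of two or three people will be imprecise and may be estimated as zero. This stands and shapes the fix.

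What none of this removes is that group delivery is described and no model or power figure allows for it.

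**Conclusion.** The point holds, conditionally and at modest size. If the pre-to-post change is positively correlated within cohorts, the Group 1 standard errors in the primary and Group 1 vs 2 models are too small and the stated power is somewhat high. With about four cohorts per campus and an assumed ICC of 0.02 to 0.10, the standard error is understated by a factor of 1.015 to 1.07. The larger effects, up to 15.5% type I error and 69% power for Group 1 vs 2, need both the upper-bound cluster size and the highest ICC assumed, and should not be read as the expected case.

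Nor do the documents support the inference that the primary aim is underpowered. In every row of the table the paired detectable difference stays below the 5% target, although at m = 10 power for that target falls to 94% at ICC 0.05 and 87% at ICC 0.10 (subject-level df). Groups 1 + 2 vs 3 is barely affected.

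The conclusion rests on an ICC and a cohort size that the article does not give, and on SDs back-solved from its power statements. The change is worth making because it is cheap, and because the direction of the error is known for any positive ICC.

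**What to change.** In the primary and Group 1 vs 2 models:

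1. Add a DPP-cohort random effect that acts on Group 1's post-enrolment change only (a partially nested model), with small-sample degrees of freedom such as Kenward-Roger. If the variance component cannot be estimated, use cluster-robust standard errors by cohort with a small-sample correction, and state that rule in advance.
2. Include campus-by-period as a fixed effect. A campus main effect alone would not reach the change.
3. Restate the power over a stated range of ICC and Group 1 members per cohort, and give the SDs used.

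The change needs no added participants. The Coordinating Center already manages the cohort data, and campus is known. The costs are slightly wider intervals, a slightly lower stated power and an imprecisely estimated cohort variance. If it turns out that only one cohort per campus contributes Group 1 members, cohort and campus-by-period cannot be separated; the report should then say that inference is limited to these five campuses and cohorts.

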
We will also compare outcomes between UC beneficiaries in Groups 1 vs. 2, a between-subject comparison, to estimate DPP effectiveness while holding the effect of the prediabetes awareness campaign constant across groups (both Group 1 and 2 receive prediabetes outreach letters). The mixed effects models mentioned above will be modified to examine between group differences in within-person change by incorporating an interaction term with Group membership. Similarly, we will compare outcomes in Groups 1 + 2 vs. Group 3, a between-subject comparison akin to an intent-to-treat (ITT) analytic approach since outcomes are being assessed among all UC beneficiaries with documented prediabetes eligible to receive the UC DPP Initiative in comparison to similarly overweight/obese individuals not exposed to the program. We will use propensity score matching to identify comparable overweight/obese beneficiaries with (Groups 1 + 2) and without (Group 3) documented prediabetes. The propensity score model will include baseline age, gender, race/ethnicity, BMI, and medical co-morbidities. Matching will be accomplished through use of the nearest-neighbor algorithm. Between group balance in the propensity scores and covariates will additionally be examined. While Groups 1 and 2 have an easily defined baseline for differentiating between pre- and post- diabetes awareness (i.e., enrollment or awareness letter date), Group 3 will have their baseline selected as corresponding to 12–18 months (or 24–30 months) prior to their most recent EHR entry.

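### In the exploratory Group 1 models, sessions attended is treated as a beneficiary characteristic, so an attendance association would be read as heterogeneity of treatment effect

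*Protocol article*

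**What the plan says.** All of this is in the protocol article, Methods, Data collection & statistical analyses.

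- **Primary model.** It is fitted within Group 1: "A fixed effect of time-period will be used to estimate the average between time-period difference in % weight change". A companion model compares the rate of change between periods. Neither includes sessions attended.
- **Exploratory extension.** "For both models, exploratory post-hoc analyses will also consider additional subject level covariates". The list runs through age, gender, race, ethnicity and co-morbidities and also contains "number of DPP sessions attended, education level and years employed at the institution", with DPP site added.
- **Effect modification.** "Interactions of the difference over time (rates or mean levels) by these subject characteristics or site will also be explored", the stated purpose being "to evaluate whether there is a differential benefit of the program for certain groups of beneficiaries", which the article equates with heterogeneity in treatment effect.
- **Follow-on rule.** The trigger is p < 0.05, and the consequence is worded as "interactions, the models will be stratified so as to allow for potential heterogeneity in the covariates as well".
- **Group 1 vs. 2.** The models "will be modified to examine between group differences in within-person change by incorporating an interaction term with Group membership". Sessions attended is not named there. The propensity score for Groups 1 + 2 vs. Group 3 uses baseline variables only.

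**The concern.** Age, race or education describe who a person was before the program. Sessions attended describes what happened to that person in the program. It has no value at enrollment, it is the dose of the intervention, and it may partly result from early success.

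The plan nevertheless gives it the same three steps as a baseline trait: adjust, test the interaction and read it as differential benefit, then stratify. For a baseline trait, that reading is a meaningful exploratory question. For attendance it is the wrong reading even if the estimate is precise. People who keep coming because they are losing weight would appear as a subgroup for whom the program works better.

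The article itself gives reasons to expect such an association:

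- Table 1 cites a university medical center worksite study in which session attendance predicted reaching the 5% weight-loss goal. That study does not settle the direction.
- The analysis section accepts that attrition may be a consequence of weight. If attrition includes leaving the program, the same feedback shortens the session count.
- Table 2 and Aim 2 name DPP participation beside % weight change when describing effectiveness, so an effectiveness measure is also being used as a modifier.

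At stake is a secondary message of the evaluation: who benefits, and therefore whom to recruit.

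**Working it through.** **Inputs.** From the article: Group 1 N = 50, Group 2 N = 500, a 5% loss in Group 1, a 2% loss in Group 2, and engagement thresholds of 9 and 16 sessions. No SD is given. The stated 90% power for a 3% difference with 50 vs. 500 implies SD 6.23, so 6.2 is used. As a check on the plan's own figures, 80% power at a 3.3% paired difference with N = 50 implies an SD of the difference of 8.16, which gives 98.9% power at 5%. The stated figure is above 98%, so it reproduces. None of these figures involves sessions attended.

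Assumed, not from the article: sessions in Group 1 with mean 14 and SD 4, and a correlation r of 0.3 to 0.5 between attendance and weight loss. Weight change is negative for loss.

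**Step 1: main effect only.** Write person i's value as a + b × period + c × sessions, with period 0 before and 1 after enrollment. Sessions has one value per person, so the post minus pre difference is b and c cancels. In 400 simulated data sets per scenario, with one pre and one post value per person, the period effect was about -5.0 with and without sessions in every scenario. Adjustment as such does no harm to this contrast.

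**Step 2: the interaction.** Suppose sessions have no causal effect and early response alone drives attendance. The expected apparent effect per session is r × 6.2 / 4:

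- r = 0.3: 0.465 points per session. From 9 to 16 sessions: 7 × 0.465 = 3.3 points.
- r = 0.5: 0.775 points per session. From 9 to 16 sessions: 7 × 0.775 = 5.4 points.

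This would be labelled heterogeneity of benefit although, by construction, attending more sessions does nothing.

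**Step 3: what the period coefficient then means.** With sessions uncentred it is the effect at zero sessions, which nobody in Group 1 is meant to represent. Its expected value is -5 + r × 6.2 × 14 / 4 = -5 + 21.7r.

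| Scenario | Formula | Simulated, uncentred | Simulated, centred |
|---|---|---|---|
| Sessions unrelated to weight | -5.0 | -5.3 | -5.0 |
| Sessions carry 3 points of the effect | -5 + 14 × 3/14 = -2.0 | -2.0 | -5.0 |
| Early response drives attendance, r = 0.3 | +1.5 | +1.6 | -5.0 |
| Early response drives attendance, r = 0.5 | +5.9 | +5.9 | -5.1 |

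Centring restores the average effect. It does not repair the reading in step 2.

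**Step 4: the Group 1 vs. 2 model, if sessions were carried over.** The article does not say this will be done. Sessions would be zero for all of Group 2. A person-level main effect again leaves the group-by-period coefficient unchanged (for example -3.03 with and without it). A sessions-by-period term fitted beside group-by-period makes the group coefficient the effect at zero sessions, -3 + 21.7r. The formula gives +3.5 and +7.9 at r = 0.3 and 0.5; the simulation gave +3.8 and +7.9. With other assumed inputs (SD 6.1, sessions mean 12 and SD 5) the formula is -3 + 14.64r, or -1.5, -0.1, +1.4 and +4.3 at r = 0.1, 0.2, 0.3 and 0.5.

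**The case against.** The best defense has three parts.

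1. **Status.** The use is labelled exploratory and post-hoc, and no primary or stated between-group estimate contains the variable. This stands and limits the weight of the point. It does not dispose of it: the label warns about chance findings and multiplicity, not about misreading a post-enrollment variable, and these are the models the article assigns to the question of differential benefit.
2. **Legitimacy.** Relating weight change to attendance is a proper question in a RE-AIM evaluation, where engagement is a planned metric. This also stands. The objection is to the label and the stratification rule, not to looking at attendance.
3. **Assumed inputs.** The article does not say that weight response drives session counts; it says so only of attrition. The session mean, SD and correlations are assumptions. This stands, so the figures above are illustrations.

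A reader might go further and infer that adjusting for sessions removes or reverses the DPP effect. The documents do not support that. The listed models are within Group 1, where a main effect cancels from the pre/post contrast. Reversal needs an uncentred interaction read at face value, or a sessions-by-period term in the Group 1 vs. 2 model, and the text specifies neither.

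**Conclusion.** The point holds as a fault of classification and interpretation in the exploratory Group 1 analyses. Applied as written, the plan would report an attendance association that reaches p < 0.05 as a treatment effect that differs between types of beneficiary, and would stratify on it. That conclusion needs no assumption about the size or direction of the association; it follows from the variable being measured after enrollment. How large a spurious gradient could be does depend on assumptions: about 3 to 5 points between 9 and 16 sessions under those used here, and none if attendance and weight change are unrelated. The invariance of the main-effect model was checked for balanced data and for the period contrast. Sample size, power, the primary result and the stated between-group comparisons do not change. The point is modest in weight and worth correcting because the correction is nearly free.

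**What to change.** - Limit the exploratory covariate, interaction and stratification list to variables fixed at baseline, plus DPP site, and take sessions attended out of it.
- Report attendance separately, as a descriptive association with weight change within Group 1. If it is modelled, centre it, and state that early weight loss may influence attendance. Call the result an adherence or dose-response association, not heterogeneity in treatment effect.
- Add one sentence that sessions attended does not enter the Group 1 vs. 2 model, since it is zero throughout Group 2 and a sessions-by-period term could distort the group effect.

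The cost is one item removed from a list and two sentences added. Aim 2 already plans to report attendance, so no information is lost, and no data collection or sample size changes.

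### Subgroup interactions within Group 1 alone are labelled heterogeneity in treatment effect, and any p < 0.05 among 18 unadjusted tests triggers stratified models

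*Protocol article*

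**What the plan says.** In the protocol article, Data collection & statistical analyses, the primary models "compare percent weight change within Group 1 subjects 12 and 24 months before DPP enrollment (pre period") with the same spans after enrolment. There are two: one for the rate of percent weight change and one for its mean level.

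The text continues: "For both models, exploratory post-hoc analyses will also consider additional subject level covariates". The list is "age, gender, race, ethnicity, number of co-morbidities, number of DPP sessions attended, education level and years employed at the institution), as well as DPP site". Then: "Interactions of the difference over time (rates or mean levels) by these subject characteristics or site will also be explored". The stated purpose is to "evaluate whether there is a differential benefit of the program for certain groups of beneficiaries (i.e., heterogeneity in treatment effect") and across sites. Where p < 0.05 is found for "interactions, the models will be stratified so as to allow for potential heterogeneity in the covariates as well". No adjustment for the number of tests is stated.

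The next paragraph modifies the models to compare Groups 1 and 2, examining "between group differences in within-person change by incorporating an interaction term with Group membership". It names no term that combines a characteristic, period and Group.

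**The concern.** Heterogeneity in treatment effect means that the difference between having and not having DPP varies across subgroups. A characteristic-by-period interaction among enrollees contains only the first half of that contrast. If older enrollees, say, would have shown a different shift around enrolment without DPP (through regression to the mean, concurrent care or metformin), the test credits that shift to the programme.

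The article recognises such influences. Aim 1 includes Group 3 to account for secular trends and concurrent programmes. The sample size section assumes a 2% loss in Group 2 without DPP and expects some beneficiaries to seek metformin.

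Two features add to the problem. The number of sessions attended is determined after enrolment, so it is not a baseline effect modifier. And the p < 0.05 rule, applied to many tests in about 50 people, lets chance decide which stratified models are fitted. Consistency across sites and key subgroups is a planned output (Table 2 and Aim 2), so readers will look for who benefits.

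**Working it through.** **Inputs.** From the sample size section: Group 1 N = 50 (10 at each of 5 sites), Group 2 N = 500, two-sided alpha 0.05, 80% power for a paired difference of 3.3%, and more than 98% power for 5%. From the analysis section: 8 characteristics + site = 9 factors, in 2 models. The standard deviation (SD) is not given.

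**The plan's own figure.** Solving the paired t-test (noncentral t) for 80% power at 3.3% with n = 50 gives an SD of paired differences of 8.16. Power at 5% is then 98.9%, so the stated figure reproduces. With n = 40 after 20% loss, the SD is 7.26 and power at 5% is again 98.9%.

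**Number of tests.** 9 x 2 = 18. Expected false positives with all nulls true: 18 x 0.05 = 0.9.

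**Chance of at least one false positive**, treating the nine factors as independent of each other:

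| Correlation between the two models, same factor | Chance |
|---|---|
| 0 | 1 - 0.95^18 = 60.3% |
| 0.5 | 57.5% |
| 0.8 | 51.7% |
| 0.95 | 45.1% |
| 1 (models always agree) | 1 - 0.95^9 = 37.0% |

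The middle rows are simulated.

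**Precision.** For a 25/25 split with SD 8.15, the standard error of the interaction is 8.15 x sqrt(1/25 + 1/25) = 2.31 points. The subgroup difference detectable with 80% power is 6.6 points, and power for a 3.3-point difference is 29%. Between two sites of 10, the detectable difference is about 10.8 points. The between-group figures (80% power at 2.5%, 50 versus 500) imply a smaller SD of about 6.0. With that value, the 25/25 split detects 4.9 points and has 48% power for 3.3.

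**Rejection with equal programme benefit.** Assume that the untreated pre-to-post change differs by d points between two equal halves of Group 1 and that DPP works equally in both. The article gives no value for d. With SD 8.15:

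| d | Significant in the direction of d (2.5% if d = 0) | Significant in either direction (5% if d = 0) |
|---|---|---|
| 1 | 6% | 7% |
| 2 | 13% | 14% |
| 3 | 25% | 25% |

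**Cost of adding Group 2.** With equal SD and a 50/50 split in both groups, the three-way standard error is 8.15 x sqrt(2/25 + 2/250) = 2.42. The ratio to 2.31 is sqrt(1 + 50/500) = 1.049, about 5% larger whatever the SD.

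**The case against.** The article calls these analyses exploratory and post hoc. Familywise error is a standard for confirmatory claims, so a formal multiplicity correction here is a matter of preference. That stands. It does not turn a one-group contrast into a treatment-effect contrast, and the stratification rule is still stated.

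Each person is their own control, so subgroup differences in stable weight trends cancel. That also stands. A reader might infer that any subgroup with a different natural trend would be misread as benefiting, but only differences in how the untreated course shifts around enrolment remain.

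The values of d are assumptions. A d of 2 or 3 points is as large as the whole assumed Group 2 loss (2%) or the whole assumed between-group difference (3%). At 1 point the excess over nominal is small.

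Table 2 and Aim 2 speak of effectiveness within and between subjects alongside consistency across subgroups, so a between-group subgroup analysis may be intended, with details left to a fuller plan. That is possible. Yet the heterogeneity label is attached explicitly to the within-Group 1 models, and the between-group paragraph names only a Group interaction.

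Finally, Group 2 chose not to enrol, and its baseline may be the letter date rather than enrolment. The propensity matching described is for Groups 1 + 2 versus 3. A three-way term therefore still mixes effect heterogeneity with subgroup-specific selection into DPP. This limits the remedy and must be stated with it.

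**Conclusion.** The point holds for an exploratory, secondary question. As written, the Group 1 interactions identify predictors of pre-to-post weight change and do not identify differential benefit, although the comparison with Group 2 is already planned.

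The 18 unadjusted tests carry a 37% to 60% chance of at least one false positive if all nulls hold. The range depends on how far the two models agree and takes the nine factors as independent; correlation among the factors would usually lower it. Power for plausible subgroup differences is low, so a significant interaction has a substantial chance of being spurious or exaggerated. The 6%, 13% and 25% rejection rates rest on assumed untreated differences of 1, 2 and 3 points and on the SD implied by the stated power.

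Two stronger readings go too far. A reader might infer that spurious subgroups are bound to be reported as differential benefit, but the article says only that interactions will be explored. A reader might also infer that the stratified models would replace the primary estimate. The article does not say so, and the primary Group 1 result is unaffected.

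**What to change.** 1. For baseline characteristics and site, test heterogeneity in treatment effect as characteristic x period x Group in the planned Group 1 versus Group 2 model. State that Group 2 is self-selected, so the contrast reduces the bias and does not remove it.
2. Report Group 1-only interactions, including sessions attended, as exploratory predictors of weight change.
3. Remove the rule that p < 0.05 leads to stratified models. Report every interaction estimate with its confidence interval from one model, and state the number of tests. False discovery rate control is optional.

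The cost is a few sentences in the analysis plan and some further modelling of data already planned for collection. Interaction standard errors rise by about 5%, and fewer nominal subgroup findings should be expected.
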